**2.5. Population studied**

The purpose of this study is to examine stress during emergency dispatch scenarios.

The population studied was CHR Metz-Thionville (Hôpital de Mercy) Centre 15 staff, including ARMs (emergency medical assistants), emergency doctors and general practitioners who met the eligibility criteria for inclusion.

**2.5.1. ARMs - their general mission**

ARMs are hospital employees who carry out a specific task in managing emergency medical assistance and continuous care requests which reach the SAMU (French Emergency Medical Assistance System) Centre 15 call dispatch centre.

These employees jointly carry out the missions they have been assigned under the legislative and regulatory framework and are under the operational supervision of dispatch and hospital doctors and general practitioners. ARMs continuously report their actions to the foregoing.
They are responsible for control room equipment and keeping all SAMU Centre 15 documentation - such as the patients identified, emergency plans, rotas, operational directories, etc. - up to date.

**2.5.2. ARMs – general skillset**

ARMs must be able to:

- Understand the organisational structure and mission behind emergency medical assistance.
- Receive all calls.
- Weed out - via brief yet specific questioning - non-medical calls, processing the relevant enquiries and prioritising them based on the degree of emergency.
- Detect life-threatening emergency situations.
- Manage communications and adapt to callers' reactions and levels of stress.
- Pass on all relevant information to dispatch doctors.
- Apply decisions per response procedure and as indicated by dispatch doctors.
- Understand the whole of operational procedures and documentation involved for daily dispatch scenarios as well as for crisis events.
- Understand what resources are available at the pre-hospital and hospital level for the French department (similar to a British county), region and the zone of defence.
- Understand the criteria used to diagnose the severity of major emergency pathologies and emergency care actions and procedures.
- Have a full command over information, communications and IT tools.
- Be capable of completing the operational and administrative documents linked to the incidents being processed as well as ensuring the operational maintenance of the dispatch centre.

**2.5.3. The role of dispatch doctors**

**The role of emergency doctors:**

- Identifying P0 and P1 (call priority) incidents
- Identifying B assessments
- Dealing with requests for inter-hospital transfers
- Dealing with requests from other SAMUs
- Dealing with SMUR requests
- Operations on public roads
- SMUR assessment

**The role of general practitioners or non-emergency care hospital doctors**

- Identifying P2 incidents
- Responding to requests for medical advice
- Dealing with calls related to continuous outpatient care

**3. Research objectives:**

**3.1. Main objective:**

Describe biological stress via cortisol levels as well as perceived stress via a visual analogue evaluation for stress in ARMs and doctors when processing a call at Centre 15.

**3.2. Secondary objectives:**

- Compare levels of both perceived and biological stress in ARMs amongst the various shifts

- Study the difficulty of the tasks required of the various ARM shifts

- Study the correlation between perceived and biological stress

- Study the correlation between the severity of the situation being dealt with over the phone and stress

**4. Research design**

This was a controlled physiological study carried out in healthy human beings, with each subject acting as their own witness.

Four experimental conditions were used for ARMs whilst two experimental conditions were used for emergency care doctors and private practitioners.

**4.1. Clear statement of the** **main evaluation criteria AND, where applicable, secondary evaluation criteria**

- Main evaluation criteria

**Objective measurement of stress: salivary cortisol assay under various experimental conditions.**

4 experimental conditions should be applied to ARMs: "call, action, evaluation, witness"

2 experimental conditions should be applied to doctors: "call, witness"

- Secondary evaluation criteria

**Subjective measurement of stress:**

**- ASA: acute stress assessment**

Acute stress assessment via the ASA form should be carried out concomitantly to each series of salivary cortisol samples being taken. This assessment form requires each subject to rate their level of stress on a scale of 0 to 10. The ASA has been validated for studies on stress (133, 134, 135, 136, 137).

**- PNOSI questionnaire: Positive and negative occupational stress inventory: chronic stress assessment**

The PNOSI chronic stress questionnaire should be completed only once by each subject. It will be distributed at 10:00 in the morning in Centre 15 (at the start time of the study) to the whole of participants that day and prior to taking any salivary cortisol samples (138, 139, 140).

**- NEO PI-R personality test: (the revised NEO personality inventory) (141): evaluating subjects' individual personality components.**

The NEO PI-R personality test should be completed only once by each subject. It will be distributed during working hours, with participants being given time off duties to complete the inventory.

This questionnaire contains 180 questions for participants to answer and is supervised by the Mercy CHR occupational psychologist. Once completed questionnaires will then be analysed by said occupational psychologist.

## 4.2. Description of the research methodology including a schematic presentation covering scheduled visits and testing.

- **Pre-inclusion visit**

The pre-inclusion visit should take place between *30 days* and no later than *15 days* before the inclusion visit.

Information on study progress and objectives will be presented by the investigator.

All PARMs (medical emergency dispatch centre call assistants) and doctors should attend this meeting.

- **Inclusion visit**

A questionnaire containing study eligibility criteria will be distributed to every ARM and unit doctor in addition to an information note on the study itself and an informed consent form.

After this visit only eligible individuals who have signed and submitted an informed consent form may participate in the study.

- Monitoring visits

**During these visits salivary cortisol assays will be performed and the relevant questionnaires (ASA and PNOSI) will be completed.**

**4.2.1. CHR METZ-THIONVILLE Centre 15 organisational structural and experimental conditions being assessed**

ARMs work 12-hours shifts every night with rotation happening every two hours, followed by three days off for a total of 36 hours a week.

Emergency doctors also work 12 hour shifts for a total of 48 hours a week, however they rotate between the medicine department, dispatch and SMUR/resuscitation.

Private practitioners more often than not work shifts of 12 hours.

The operational structure of Metz Centre 15 is as follows: medical dispatch assistants (ARMs) are assigned to one of three areas:

- **Call ARMs** provide the first line of support, answering all incoming calls. They assess the severity of the situation at hand and, based on this information, transfer the call to either an emergency doctor or a general practitioner. This position is the most stressful of the three.

- **Action ARMs** provide various means of intervention. This area organises patient transport and is responsible for ringing up ambulances, the fire brigade or SMUR teams based on what is required for the matter at hand. They only act once they have received due instruction from either a general practitioner or emergency doctor.

- **Assessment ARMs** are in charge of collecting reports from the various dispatch assignments.

The way the doctors work however is quite different. Call ARMS send independent practitioners (who are more often than not general practitioners) less serious calls which still require medical advice or just an ambulance. Emergency doctors manage the more severe situations which require more in the way of support; they are the only ones who can authorise an SMUR dispatch, as an example.

This study will be conducted by including the same number of experienced ARMs (i.e. those with over five years of experience) as younger ARMs (i.e. those with less than five years' experience). The same dispatch assistant will also be studied whilst working in each of the three areas.

During this study one call will firstly be studied, which will act as the control or reference. A series of salivary cortisol samples will then be taken from the call ARM at that time. The first sample will be taken when the ARM hangs up the phone, which is the T0 sample. Additional samples will then be taken every 15 minutes over 90 minutes, with the final sample being taken at two hours from T0. Once the call is transferred to the doctor - either the emergency doctor or SMUR doctor - samples will be taken from the doctor in question, with T0 being the moment when the doctor ends the call and takes the swab. The same call will be studied in exactly the same way for action ARMs and assessment ARMs.

All calls will be studied in this way.

**4.2.2. Practical organisation of the study**

.

***SALIVARY CORTISOL ASSAYS***

***Materials***

The assay will be carried out using Biomnis or Sarstedt Salivette swabs in combination with ASA subjective stress measurements.

Swabs will be provided by either Biomnis or Sarstedt and consist of a cotton tip which must be thoroughly soaked with saliva, which is achieved by biting down on for two or three minutes (see the annexes for more information). Samples will then be rendered anonymous and coded for confidentiality purposes. The swabs will then be stored in a Mercy Hospital laboratory freezer at -4 degrees Celsius for local analysis later. Samples may be stored at a temperature of -4 degrees Celsius for one year.

***Experimental conditions***

Salivary cortisol will be collected for each ARM over three working days in three different positions: calls, resource deployment or action, and assessment.

Participants will be notified of proper sampling conditions for the salivary cortisol assay. Once enrolled on the study participants shall undertake not to drink or eat anything for half an hour prior to the sample being collected as well as during the two hours when samples are taken. Subjects must also agree not to smoke thirty minutes prior to samples being taken as well as during the sample collection period. Regarding other variation factors which affect salivary cortisol levels, light levels will not vary over the working day and subjects will be working in a seated position, so standing will not be accounted for.

Calls assays will be taken for will be for the same time period to prevent any bias arising in terms of inter- and intra-individual circadian variations in salivary cortisol levels.

The first incoming call for the ARM shall be used as the reference, however accidental or mistaken calls will be excluded from the study. During the call, a salivary control assay will be taken for the call ARM, with the first assay being marked T0. Additional assays will be conducted for call ARMs every 15 minutes after T0 for 1 hour and 30 minutes, followed by a final assay at two hours after the call, which translates to eight assays which will be used to generate the acute stress curve. Cortisol assays will all be carried out at the same time to prevent nycthemeral variations. Each sample will be taken as soon as the subject ends the call and hangs up the phone.

The same salivary cortisol assay following the same principle will then be carried out on the doctor the call was transferred to. The same assay will also be carried out on the action ARM and the assessment ARM. The next day the salivary cortisol assay will be carried out on the same ARMs but as assigned to different areas.

Three medical dispatch assistants should therefore have salivary cortisol assays administered every day as should a doctor - either an emergency doctor or independent practitioner - based on the severity of the call.

Each additional call will be noted when taking salivary cortisol measurements. Each event over the two hour sampling period will likewise be recorded to prevent any bias arising and for a better understanding and analysis of the curves generated.

Salivary cortisol assays should likewise be administered on days off (the day after a working night shall not be deemed to be a day off) to obtain reference values and limit intra-individual variation.

This assay will be carried out per a different methodology as the purpose here is not studying acute events but rather for the generation of a reference curve. Eight samples shall be taken at regular intervals over the course of the day. The first sample will be taken when the subject wakes up and shall be used as T0, followed by samples taken every two hours. Samples should be stored at room temperature by participants and then taken to the CHR the next day. Each participant will be provided with an explanatory note.

Saliva samples will be made anonymous. Each subject shall be assigned a number for each time an individual sample was taken.

Samples shall be stored at -4 degrees Celsius in a dedicated freezer, which has been kindly provided by the Mercy Hospital laboratory. Samples will then be analysed in the Mercy CHR laboratory at a later date.

**4.2.3. Completing the stress evaluation questionnaires**

* PNOSI (chronic stress): this should be completed once by each subject at Centre 15 at 10:00 in the morning (when the study officially starts) and prior to having the first salivary cortisol samples taken.

* ASA (acute stress): this questionnaire shall be completed concomitantly with each cortisol assay. Each subject shall rate their level of stress on a scale of 1 to 10.

* NEO PI-R (personality test): this should be completed once by each subject at Centre 15 and under the supervision of the Mercy CHR occupational psychologist.

**4.2.4 Other data collected**

Intervening events (such as other calls, specific contexts, etc.) shall be recorded during periods where salivary cortisol assays are being taken (i.e. over 2 hours per each subject).

Furthermore during each call, the gravity of the situation at hand will be assessed using the following classification to look for a correlation between physiological stress levels and the seriousness of the call.

For ARMs:

Three levels of priority shall be applied when transferring the call to a dispatch doctor:

P0: procedural response of an SMUR team being sent followed by priority dispatch

P1: priority dispatch

P2: dispatch that can be put on hold without risk to the patient until other dispatches which are currently out can arrive

For dispatch doctors:

Dispatch doctors make their decisions based on four levels of emergency:

R1: a patent or latent life-threatening emergency requiring a resuscitation team (SMUR) being dispatched.

R2: a real emergency although not life-threatening which would require the attention of a nearby doctor, ambulance or the fire brigade within a period of time contractually agreed to between the dispatcher, the acting party and the caller.

R3: access to continuous care required although the time it takes to do so presents no immediate risk; a medical prescription for later may be suggested.

R4: medical advice or drug prescription can be provided over the phone.

For assessment ARMs:

Three levels of priority are applied by ARMs when forwarding assessments to dispatch doctors:

B0: assessment with signs of distress which were not apparent during the call. This call should be answered as a priority by the emergency dispatch doctor.

B1: assessment providing additional information which was not present during the initial dispatch but absent of any signs of distress or seriousness.

B2: an assessment in line with the data collected during the call to dispatch.

## 4.3. Description of measures taken to reduce and prevent biases from arising, more specifically for the purposes of ensuring random draws and blinding methods

This study will be conduct openly and does not require a random draw.

Each subject will be their own witness. Subjects will be assessed under identical experimental conditions which are specific to their position (ARMs and medical personnel).

See point 4.2. for more information in this regard.

## 4.4. Expected length of individuals' participation

Inclusion period length: 1 month

Length of each individual's participation: four instances of two hours for ARMs and two instances of two hours for doctors.

ARMs: four instances of 8 samples each / Doctors: Two instances of 8 samples each

Total length of the study: 6 months

**4.5. Identification of all data to be recorded directly in case report forms which shall then deemed to be source data.**

Not applicable.

**5. Selection and exclusion criteria for research participaNTS**

**5.1. Inclusion criteria**

- Centre 15 medical and paramedical employees (medical dispatch assistants, emergency doctors, independent practitioners):
- Who have received information about the study
- Who have signed a consent form to participate in the study
- Who are on a compulsory membership with a social security scheme

**5.2. Exclusion criteria**

- Chronic alcoholics
- Women who are on combination oestrogen plus progestin treatment
- Pregnant women
- Highly athletic individuals
- Individuals on steroid-based medical treatment
- Individuals being monitored for psychiatric disorders (mainly depression)
- Individuals presenting with fever on the day samples are taken
- Volunteer participants who have endocrine diseases

**5.3. Early withdrawal from the study or exclusion (END OF MONITORING)**

**Criteria and procedures for ending monitoring**

- *Definitively*

Upon request of the subject

- *Temporarily*

Not applicable

**5.4. Recruitment procedures**

Metz-Thionville CHR Centre 15 medical and paramedical employees (emergency call staff, emergency doctors, independent practitioners) shall be notified this study is being carried out. Each individual employee will then be asked to participate in the study as long as they are eligible to do so per the criteria above.

*If over 20 individuals express their desire to participate in the study a random draw will be held to decide who the participants will be.*

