**8.2. Planned number of individuals to be included in the study with the statistical grounds for the number given**

This is a study where the main objective is descriptive; additionally it may serve a purpose as a feasibility study with respect to the comparative (secondary) objectives. 20 ARMs and 20 doctors (emergency doctors or independent practitioners) are expected to be included.

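### The recruitment rule in section 5.4 triggers a random draw above 20 volunteers from all staff together, so the 20 ARMs and 20 doctors planned in section 8.2 cannot be reached without triggering it, and the draw does not secure the seniority balance

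*Protocol*

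**What the plan says.** Three places in the protocol bear on who is enrolled.

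- **Section 5.4 (recruitment).** The invitation covers every staff category in one sentence: "medical and paramedical employees (emergency call staff, emergency doctors, independent practitioners) shall be notified this study is being carried out". The selection rule follows: "If over 20 individuals express their desire to participate in the study a random draw will be held". It gives no threshold by profession, no number to be drawn and no strata.
- **Section 8.2 (planned number).** "20 ARMs and 20 doctors (emergency doctors or independent practitioners) are expected to be included". The section calls the main objective descriptive and gives no effect size, SD or power.
- **Section 4.2.1 (organisation).** "This study will be conducted by including the same number of experienced ARMs (i.e. those with over five years of experience) as younger ARMs", the latter having under five years.

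Section 8.1 then plans exploratory Kruskal-Wallis comparisons of the cortisol delta, among others by ARM seniority and by doctor's status. Section 4.4 fixes the sampling load: "ARMs: four instances of 8 samples each / Doctors: Two instances of 8 samples each".

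**The concern.** Section 5.4 counts individuals directly after naming all three staff categories. Read as written, its threshold is half the planned enrolment. A site that follows it would hold a draw whenever recruitment goes well enough to meet section 8.2, and the text does not say how many to keep.

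Two things are at stake. One is the size and composition of the study: how many ARMs and how many doctors are described. The other is the equal split of senior and junior ARMs, which section 4.2.1 promises and the seniority comparison in section 8.1 draws on. Neither can be restored at analysis once the wrong people have been selected.

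**Working it through.** **Planned figure.** Section 8.2: 20 + 20 = 40. The threshold in section 5.4 is 20, and 20/40 = 0.5. Reaching 40 requires at least 40 volunteers, which exceeds 20, so the draw is always triggered on the way to the target. With 20 or fewer volunteers there is no draw, but the target is missed anyway.

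The documents give no staff or volunteer numbers. All pools below are assumptions.

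**Reading 1: 20 are drawn from everyone.** With A ARM and D doctor volunteers and a simple draw of 20, the number of ARMs, X, is hypergeometric:

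P(X = k) = C(A, k) × C(D, 20 − k) / C(A + D, 20), with mean 20 × A / (A + D).

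- A = 20, D = 20: mean = 20 × 20/40 = 10. P(X = 10) = C(20,10)² / C(40,20) = 34,134,779,536 / 137,846,528,820 = 0.248. Summing k = 7 to 13 gives 0.974.
- A = 20, D = 30: mean = 20 × 20/50 = 8; 95% range 5 to 11.
- A = 20, D = 20, with the ARMs 10 senior and 10 junior: the probability of equal senior and junior numbers is Σ C(10,k)² × C(20, 20 − 2k) / C(40,20), k = 0 to 10, which is 0.174.

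Sampling load, using section 4.4:

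| | Series | Samples |
|---|---|---|
| 20 ARMs + 20 doctors | 20×4 + 20×2 = 120 | 120×8 = 960 |
| 10 ARMs + 10 doctors | 10×4 + 10×2 = 60 | 60×8 = 480 |

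**Reading 2: 20 are drawn within each profession.** The total is 40 and agrees with section 8.2. What remains is seniority. For a simple draw of 20 ARMs from S senior and J junior volunteers, P(10/10) = C(S,10) × C(J,10) / C(S + J, 20):

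| Assumed pool (S/J) | P(exactly 10/10) |
|---|---|
| 12/12 | 0.41 |
| 15/15 | 0.30 |
| 18/12 | 0.10 |
| 20/10 | 0.006 |

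An exact split is a strict criterion, so the cost of missing it also matters. From the 15/15 pool, the split lies between 8/12 and 12/8 with probability 0.950, and between 7/13 and 13/7 with probability 0.995. With equal variances, the standard error of a senior-junior difference is proportional to √(1/n₁ + 1/n₂). Relative to 10/10:

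- 12/8: √(1/12 + 1/8) / √(1/10 + 1/10) = 0.4564 / 0.4472 = 1.021, or 2.1% larger.
- 13/7: √(1/13 + 1/7) / √(1/10 + 1/10) = 0.4688 / 0.4472 = 1.048, or 4.8% larger.

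A simple draw therefore often misses the equality stated in section 4.2.1, at little cost in precision when the pool is balanced. In the skewed 20/10 pool, the 95% range for the number of seniors is 11 to 16.

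**The case against.** The strongest reply is that the threshold of 20 equals the planned number in each group, so 20 per profession was probably meant. The literal reading makes the protocol's own target unreachable, which also suggests a missing qualifier. This is plausible and would remove the conflict in numbers. It is not what the text says, though, and a site would have to guess. It also leaves the seniority split unsecured.

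Some of the reply stands in full. Section 5.4 states a trigger and not a cap, and it does not describe the draw as simple; both are inferred from what it omits. Nothing in it forbids a draw that honours section 4.2.1. The Kruskal-Wallis test does not need equal groups, the tests are exploratory, and the 40 are an expectation with no power calculation behind it.

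Two stronger readings are tempting and should not be made. A reader might infer that section 4.3 contradicts section 5.4, because it says: "This study will be conduct openly and does not require a random draw". That sentence belongs to the section on bias and blinding, beside the statement that subjects are their own controls. It most naturally concerns randomisation in the design, not selection among volunteers. A reader might also express the loss as a wider confidence interval for the mean cortisol delta. Section 8.1 plans 95% intervals for qualitative variables only; the delta is described by mean and SD, or by median with range and interquartile interval.

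**Conclusion.** The point holds with moderate severity. On its wording, the recruitment rule conflicts with the planned sample size: 20 individuals across all staff against 40, so the target cannot be reached without triggering the draw. If 20 are drawn, which is an inference, enrolment is halved. The ARM count then becomes random, with 10 expected and 7 to 13 with probability 0.974, assuming 20 volunteers from each profession.

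If 20 per profession was intended, only the seniority balance is left open. From an assumed 15/15 pool the split would be between 8/12 and 12/8 in 95% of simple draws, which costs at most about 2% in standard error. A skewed pool would do worse, but the documents give no basis for choosing one.

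The descriptive aim and the exploratory status of the seniority comparison limit the consequence. The point still deserves correction, because selection happens before any data exist and no analysis plan can repair it.

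**What to change.** Rewrite the selection rule in section 5.4 along these lines:

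- A draw is held separately among ARMs and among doctors, and only in a group with more than 20 eligible volunteers. Twenty are selected per group.
- ARMs are drawn within seniority strata in equal numbers: 10 senior and 10 junior where volunteers allow. If one stratum has fewer than 10, the remaining places are filled from the other.
- ARMs with exactly five years of experience are assigned to a named stratum. Section 4.2.1 defines only over and less than five years.

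The cost is a few sentences, settled before recruitment opens. No participants are added beyond the planned 40. Section 9 already provides for recording whether length of service is above or below five years, so the strata ask for little that is new; it must be known before the draw. Section 4.3 needs no change on this account.
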